# SAFETY REPORTING

## Temporary halt for reasons of subject safety

In accordance to section 10, subsection 4, of the WMO, the sponsor will suspend the study if there is sufficient ground that continuation of the study will jeopardise subject health or safety. The sponsor will notify the accredited METC without undue delay of a temporary halt including the reason for such an action. The study will be suspended pending a further positive decision by the accredited METC. The investigator will take care that all subjects are kept informed.

## AEs, SAEs and SUSARs

### Adverse events (AEs)

Adverse events are defined as any undesirable experience occurring to a subject during the study, whether or not considered related to the experimental intervention. All adverse events reported spontaneously by the subject or observed by the investiga­tor or his staff will be recorded.

### Serious adverse events (SAEs)

A serious adverse event is any untoward medical occurrence or effect that

- results in death;
- is life threatening (at the time of the event);
- requires hospitalisation or prolongation of existing inpatients’ hospitalisation;
- results in persistent or significant disability or incapacity;
- is a congenital anomaly or birth defect; or
- any other important medical event that did not result in any of the outcomes listed above due to medical or surgical intervention but could have been based upon appropriate judgement by the investigator.

An elective hospital admission will not be considered as a serious adverse event.

The investigator will report all SAEs to the sponsor without undue delay after obtaining knowledge of the events.

The sponsor will report the SAEs through the web portal *ToetsingOnline* to the accredited METC that approved the protocol, within 7 days of first knowledge for SAEs that result in death or are life threatening followed by a period of maximum of 8 days to complete the initial preliminary report. All other SAEs will be reported within a period of maximum 15 days after the sponsor has first knowledge of the serious adverse events.

**8.2.3 Suspected unexpected serious adverse reactions (SUSARs)**

Conversion of the OLGB to a RYGB due to untreatable biliary reflux is expected to occur in 5-10% of patients. They will be reported through the web portal *ToetsingOnline*

## Follow-up of adverse events

All AEs will be followed until they have abated, or until a stable situation has been reached. Depending on the event, follow up may require additional tests or medical procedures as indicated, and/or referral to the general physician or a medical specialist.

SAEs need to be reported till end of study within the Netherlands, as defined in the protocol

## [Data Safety Monitoring Board (DSMB) / Safety Committee]

Based on the current experience of the surgeons with the procedures a DSMB is not

considered necessary

# STATISTICAL ANALYSIS

## Populations for analysis

## All efficacy analyses will be conducted using the full analysis set. The full analysis set will include all randomized patients with at least one post-baseline measurement and fulfilling all inclusion criteria, in accordance with the intention to treat principle (ITT).

## The Per-Protocol analysis set is defined as those patients of the full analysis set who completed the study at 60 months and are fully compliant to all exclusion criteria. The Per-protocol analysis set will be used only if the percentage of excluded patients is substantial, i.e. > 15% of the full analysis set.

## The safety analysis set consists of all randomized patients.

## All patients will be analyzed according to allocated treatment strategy, irrespective of treatment strategy actually used. For safety endpoints, analysis will be performed using the treatment strategy that was actually used. An additional “Per-Protocol analysis” will be conducted only if the Per-Protocol analysis set is defined.

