# STUDY DESIGN

This is a double-blind randomized 5 year study with two arms. Patients who are scheduled for primary OLGB surgery are eligible when during the surgery total small bowel length can be measured and when they are able to swallow the Fitforme WLS primo multivitamin capsule. Patients will be allocated to one of the two surgical treatment arms by randomization at the beginning of the operation. Only the operating surgeon is aware of the allocation and will document total small bowel length, treatment allocation and BP-length in a coded database. Both the TSBL and the length of the BP-limb will not be documented in the patient file. The investigators and the patient will not be informed on the BP-limb length during the study.

Patients with a small bowel that could not be measured during surgery will be treated according to the current daily practice and will not enter the study.

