## Randomisation, blinding and treatment allocation

After informed consent is given, the patient is asked to swallow one Fitforme WSL primo capsule. A patient who is not able to swallow the capsule will be withdrawn form the study.

Randomization is performed using a table of random figures delivered by a independent party (clinical pharmacist), using envelopes with the treatment allocation.

The envelope contains a study number on the outside and the same number with one of the treatment arms within. The envelope will be opened by the OR nurse when the surgeon has succeeded in measuring the TSBL.

If the surgeon is not able to measure the TSBL the patient will be withdrawn from the study.

The study number and the patients medical file number will be forwarded to the principle investigator by the surgeon.

The surgeon will document the allocation, total small bowel length and length of the BP-limb in the file containing only study numbers. In the follow-up neither any of the usual care medical providers nor the patient is aware of the allocation or BP-limb length. The surgeon will not describe the TSBL and the BP-limb length in his surgical report.

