## Study procedures

A standard operation protocol for OLGB will be used in all patients. The pouch will be made with the help of a linear stapler. At first, the stomach will be transected horizontally at the junction of the corpus and antrum at the level of crow’s foot. A small pouch is made with help of a calibration sonde of 34 French, the pouch is finished near the angle of His. Then the total limb length is measured. With a succesfull TSBL measurement the OR nurse will open the envelop and the allocated procedure will be communicated to the surgeon. Based on the randomization outcome biliopancreatic limb length is measured. In case the measurement of the total limb length does not succeed, standard limb length of 150 cm is performed. An antecolic, retrogastric anastomosis is performed by liniar stapling and the remaining defect is closed by V-loc. An anti-reflux stitch is performed. Integrity of the anastomoses is checked by methylene-blue-test and in case of leakage, extra sutures will be applied. The mesenterial defect of Peterson will be closed as far as possible by endo hernia stapling or unresolvable V-loc.

The extra measurements of limb length will take less than ten minutes of time. In patients allocated to standard treatment the surgeon will construct a BP-limb of 150 cm. In patients allocated to the adjustment length, the length of the BP-limb will depend on the total small bowel length : < 500 cm : 150 BP; 500-700 cm : 180 BP and > 700 cm : 210 BP.

On leave of the hospital the patients will be provided with Fitforme WSL Primo multivitamin capsules for the following period and will be instructed to use one capsule once daily.

Follow-up will take place in accordance with usual care, i.e. after 1,6,12 and 24 months and yearly up till 5 years. Extra visits will be at 18,30,42 and 54 months for compliance check and distribution of FFM multivitamins.

Weight measurements and blood samples will be taken in accordance with the standard protocol of follow-up after bariatric surgery in our institute added with 20 ml for selenium and copper measurements and future lab tests at 1,3 and 5 years.

Data from 6,12 and 24 months and every year thereafter up to five years after surgery will be anonymously collected in a database.

At each visit standard care includes :

- inquiry after well being and complaints, side effects, adverse events
- documenting current medication use, both regular and over-the-counter, and when applicable CPAP use

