### Specific criteria for withdrawal

Patients who are not able to swallow the FFM WSL primo capsule and those in whom the surgeon cannot measure the TSBL will be withdrawn from the study and will be replaced.

Patients who develop complications during the first 30 days needing revisional surgery changing bowel length will be withdrawn from the study.

Patients who need a conversion from the OLGB to a RYGB during the study will be withdrawn from the study and not replaced. They will be analysed on a intention to treat principle and all data up to the conversion will be used in the study.

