## Premature termination of the study

Reasons for prematurely termination of the study are :

an unexpectedly high rate of surgical complications due to measuring total small bowel length or adjusting the BP-limb length as to the discretion of the investigator.

An unacceptable percentage of complications like excessive weight loss, diarrhea or nutrient deficiencies in either study arms as to the discretion of the investigator .

This will be investigated, at first without unsealing treatment allocation after the first 50 and 100 operated patients (operative complications) and after 1 and 2 years after start of the study for non-operative complications. If there is a high complications rate in the whole group treatment allocation will be unsealed to investigate further.

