## Other study parameters

**Safety analysis**

All serious adverse events will be summarized and differences between study groups assessed using the same approach as specified for the quantitative secondary endpoint parameters. Relationship to study intervention, i.e. to the measurement of total small bowel length or adjusting the BP-limb length, will be presented. Furthermore, a differentiation between surgical complications and non-surgical serious complications (e.g. excessive weight loss, diarrhea or nutrient deficiencies) will be provided.

Of all non-serious adverse events only surgical complications will be presented. In this, early (within one month) and late (after one month) surgical complications will be presented separately.

All non-serious, non-surgical complications (e.g. excessive weight loss, diarrhea or nutrient deficiencies) are taken into account as secondary efficacy endpoints.

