# STRUCTURED RISK ANALYSIS

## Potential issues of concern

1. a full measurement of the small bowel length during surgery includes a small risk of laceration of the bowel. The surgeons are experienced in this technique of measuring as they need to measure the distance from Treitz to the planned anastomosis during the standard procedure of the OLGB.

2. the adjusted lengths of the biliopancreatic limb based on total small bowel length are within the currently used lengths in literature and are considered safe. Whether this leads to less or more adverse events in the patients after the surgery is part of the investigation. However, all expected side effects are treatable.

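### Patients whose small bowel measurement is started but not completed fall outside the safety set, so injuries in abandoned attempts are missing from the planned analysis of measurement-related harm

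*Protocol*

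**What the plan says.** **The risk.** The Summary, the section on known and potential risks of the surgical treatment, and section 12.1 all say that measuring the whole small bowel adds some risk of bowel damage. Section 12.1 puts it as "a full measurement of the small bowel length during surgery includes a small risk of laceration of the bowel". The section on risks also states that a longer biliopancreatic limb does not raise surgical risk.

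**The order of events.** Consent is signed before surgery (inclusion criteria; section 10.2). Section 7.2 says "The envelope will be opened by the OR nurse when the surgeon has succeeded in measuring the TSBL", and section 7.3 agrees: "With a succesfull TSBL measurement the OR nurse will open the envelop and the allocated procedure will be communicated to the surgeon". Section 3 differs: "Patients will be allocated to one of the two surgical treatment arms by randomization at the beginning of the operation".

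**Failed measurements.** Under the specific criteria for withdrawal, "those in whom the surgeon cannot measure the TSBL will be withdrawn from the study and will be replaced". Section 7.5 repeats the replacement rule, section 7.6 leaves withdrawn patients in usual care, and section 3 says that patients who cannot be measured do not enter the study.

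**The analysis.** Under Populations for analysis: "The safety analysis set consists of all randomized patients". The disposition summary in section 9 counts only withdrawals after randomisation. The Safety analysis text then promises, for serious adverse events: "Relationship to study intervention, i.e. to the measurement of total small bowel length or adjusting the BP-limb length, will be presented". Section 7.7 lists as a reason to end the trial early "an unexpectedly high rate of surgical complications due to measuring total small bowel length or adjusting the BP-limb length".

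**The concern.** A patient is exposed to the measurement risk from the moment the surgeon starts to measure. Under sections 7.2 and 7.3, that patient enters the safety set only if the measurement is completed. The set is thus conditioned on the success of the procedure whose harm it is meant to describe.

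Comparing the arms does not repair this. Every randomised patient in either arm has had a completed measurement, so a difference between arms says nothing about its risk. Only a single proportion over all attempts does, and the stated set leaves out the attempts that failed.

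At stake is the reported count, and possibly the reported rate, of a surgical harm that patients incur only because they joined the study. A later reader deciding whether to measure TSBL routinely would rely on that figure.

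**Working it through.** **1. Patient flow under sections 7.2 and 7.3**

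| Course of the measurement | Exposed to the risk | Randomised | In the safety set |
|---|---|---|---|
| Completed, no injury | yes | yes | yes |
| Completed, with injury | yes | yes | yes |
| Abandoned, no injury | yes | no | no |
| Abandoned, with injury | yes | no | no |

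Only the last two rows are lost. Injuries in completed measurements are kept, because those patients go on to be randomised.

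**2. Flow under section 3.** If allocation takes place at the start of the operation, a patient with a failed measurement would already be randomised and so inside the set. The same section, however, keeps such patients out of the study, and the withdrawal section replaces them. Section 3 therefore gives no clear route by which they would be analysed.

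**3. Inputs.** The protocol states no failure rate, no injury rate and no link between the two, so it has no figure on this point to reproduce. The one figure taken from it is the planned total of 2 × 106 = 212 (section 4.4). The rest are assumptions:
- f, the share of measurements that fail: 2%, 5%, 10%
- k, the injury risk in failed relative to completed attempts: 1, 3, 10
- p, the injury risk in completed attempts: 1% (needed only for step 6)

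**4. Exposed patients outside the set.** Attempts = 212 / (1 − f); failed = attempts − 212.
- f = 2%: 212 / 0.98 = 216.3, so 4.3 failed
- f = 5%: 212 / 0.95 = 223.2, so 11.2 failed
- f = 10%: 212 / 0.90 = 235.6, so 23.6 failed

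**5. Share of measurement injuries missed.** Share = f·k / (f·k + 1 − f). The risk p cancels.

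| | f = 2% | f = 5% | f = 10% |
|---|---|---|---|
| k = 1 | 0.02/1.00 = 2% | 0.05/1.00 = 5% | 0.10/1.00 = 10% |
| k = 3 | 0.06/1.04 = 6% | 0.15/1.10 = 14% | 0.30/1.20 = 25% |
| k = 10 | 0.20/1.18 = 17% | 0.50/1.45 = 34% | 1.00/1.90 = 53% |

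**6. Effect on the rate.** The safety set shows p. The rate over all attempts is p·(1 − f + f·k). With p = 1%:
- k = 1: 1.0% for every f, so no bias
- k = 3: 1.04%, 1.10%, 1.20%
- k = 10: 1.18%, 1.45%, 1.90%

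The count is too low whenever k is above 0. The rate is too low only when k is above 1.

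**7. Absolute numbers.** With p = 1%, the safety set is expected to hold 0.01 × 212 = 2.12 injuries. The expected number outside it is p·k × failed. That is 0.04 at the low corner (f = 2%, k = 1: 0.01 × 1 × 4.3) and 2.36 at the high corner (f = 10%, k = 10: 0.01 × 10 × 23.6).

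**The case against.** The strongest reply is that these events need not be lost to the trial. Patients have consented before the operation. Section 8.2.1 defines adverse events for any subject during the study, and section 8.2.2 sends all serious events to the sponsor and on to the ethics committee. A laceration that makes the surgeon stop happens before the withdrawal that it causes. The Safety analysis text also begins by covering all serious adverse events, without itself limiting them to randomised patients. This stands as far as recording goes. It does not settle the analysis, because the defined safety set would normally govern that text. Nor does it cover an injury that shows itself only after the patient has returned to usual care.

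A reader might infer that the stopping review is biased as well. The documents do not support that. Section 7.7 does not mention the safety set. It looks at the first 50 and 100 patients operated on, and a patient with a failed measurement still has the operation. The section does not say whether such patients count, so an effect is possible but not shown.

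A reader might also infer that injuries concentrate in failed attempts, so that the reported rate must be too favourable. A difficult or injured bowel is a plausible reason to stop measuring, but no section gives data on this. The exclusion of patients whose earlier abdominal surgery prevents measurement should remove some difficult cases beforehand.

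Finally, the primary endpoint and the between-arm safety comparison are untouched. That is correct, and it limits the weight of the point.

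**Conclusion.** The point holds in a limited form, as something that should be fixed, with moderate confidence. Under sections 7.2 and 7.3, consented patients exposed to a risk that the protocol itself names are left out of the set used to report it whenever their measurement is abandoned. The measurement-related safety analysis then under-counts injuries if abandoned attempts cause any harm at all.

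The size is unknown, because the protocol gives no rates. Over the assumed ranges the share missed runs from 2% (2% failure, equal risk) to 53% (10% failure, tenfold risk). The upper figures depend on the assumed tenfold risk ratio and should not be quoted without it. A downward bias in the rate needs a higher risk in failed attempts, which is plausible but undocumented.

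Confidence is moderate because section 3 conflicts with sections 7.2 and 7.3 on the timing of randomisation, and because event recording may capture part of what the analysis set leaves out.

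**What to change.** 1. **Populations for analysis:** add a descriptive safety set for operative and measurement-related complications, made up of all consented patients in whom TSBL measurement was started, whether or not it was completed. Keep all randomised patients as the set for the between-arm safety comparison.
2. **Safety analysis and section 7.7:** name this set as the denominator for measurement-related complications, and say whether failed measurements count towards the reviews after 50 and 100 operations.
3. **Specific criteria for withdrawal and sections 7.5 and 7.6:** keep patients with a failed measurement in adverse-event recording for 30 days, although they are replaced for efficacy. This fits the 30-day window already used for replacement and the one-month boundary between early and late surgical complications.
4. **Section 3 against sections 7.2 and 7.3:** reconcile the timing of randomisation, so that it is clear who counts as randomised.

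The cost is wording in these sections and event records for a few extra patients (about 4 to 24 under the assumed failure rates) who are in routine postoperative care anyway. The reported complication rate may come out less favourable. Treatment, sample size and efficacy analysis do not change.

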## Handling of missing data

## Missing data will remain as missing, and no attempt will be made to estimate or replace missing values. Only observed values will be used in data analyses and presentations.

## Patient demographics and other baseline characteristics

## A schematic summary of the number of eligible patients enrolled and randomized will be presented by treatment strategy group. The number of subjects withdrawn from the study after randomization will be tabulated by treatment strategy group. The time and reason for withdrawal will be listed by treatment strategy group. Potential biases due to withdrawal of subjects will be investigated.

## A complete baseline description of the patients' demographics and disease characteristics will be tabulated by treatment strategy group for the full analysis set. This includes demographics (e.g. age, gender, race) and a detailed baseline description including general medical history, disease specific medical history (including risk factors), physical examination (e.g. weight, height), vital signs and relevant concomitant medication. The baseline values of study endpoints, where applicable, will be included in the presentation of the baseline description.

## Statistical differences will not be formally evaluated. If differences are considered clinically relevant, caution will be taken when interpreting the results of the analyses between groups and the statistical methods may be modified to adjust for this difference. (By definition, differences between the randomised treatment groups at baseline are due to chance only.)

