## Sample size calculation

The null hypothesis in the study is as follows : the percentage TWL at five years in both groups is not different with a mean of 35. The alternative hypothesis is that the mean of the absolute difference in TWL in the experimental group is 5% more than the standard group (40% and 35% respectively).

For the evaluation of the primary endpoint of the percent total weight loss (%TWL) at five years, a sample size of 2x 92 will achieve 80% power to detect a (absolute) difference of -5.0% between the null hypothesis ( both group means of %TWL are 35.0) and the alternative hypothesis (mean of experimental group is a %TWL of 40.0) with estimated group standard deviations of 12.0 and 12.0 and with a significance level (alpha) of 0.05 using a two-sided two-sample t-test.

In case of a reduced standard deviation in the active treatment group of 9.0, the power achieved is 88.8%.

With an expected maximum drop-out due to conversion of OAGB to RYGB of 15% the sample size is 92 plus 14 = 106 patients in each group, leading to a total of 212 participants in the study.

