## For qualitative parameters (categorical or ordered), frequency counts and percentages of each category will be calculated by treatment group. Percentages will be reported up to 1 decimal place.

## Primary study parameter(s)

The primary null hypothesis for this study is that there is no significant difference in the mean change in the percent of total weight loss (%TWL) at five years, between patients treated with a TSBL adjusted BP limb length (active group) versus patients treated with a standard BP limb length of 150 cm (control group).

In addition to the descriptive statistics (see the above section : Patient demographics other baseline characteristics), the two treatment strategy groups will be compared using two-sample T-test if parameter is normally distributed. Visual inspection of the distribution, as well as the Shapiro-Wilk test for normality, will used to assess normality. Unless equality of variance between groups is established, the Satterthwaite method for t-statistics and 95% confidence intervals will be used. If data is skewedly distributed, a Mann-Whitney U-test (Wilcoxon two-sample test) will be applied. For the difference in medians, the Hodges-Lehmann estimate will be used with distribution-free 95% confidence intervals.

In addition to the above mentioned analyses, the homogeneity of treatment effect over different strata of patients will be evaluated. In this, differences in treatment effect over separate strata of potentially relevant factors (e.g. gender, baseline BMI, co-morbidities, compliance, etc) will be evaluated. A multivariable model will be used to formally establish homogeneity, i.e. the absence of effect modification for the potentially relevant factors, separately.

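### The primary 5-year %TWL test is valid but unadjusted, and an undefined clause lets the method change if baseline differences look relevant

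*Protocol*

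**What the plan says.** Protocol section 9, Primary study parameter(s): "the two treatment strategy groups will be compared using two-sample T-test if parameter is normally distributed". If variances are not shown to be equal, the Satterthwaite form applies. If the data are skewed, a Mann-Whitney test with a Hodges-Lehmann estimate is used. No covariate enters the comparison. A multivariable model appears later in that section, but it looks for effect modification one factor at a time and does not adjust the primary estimate.

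The Sample size calculation rests on the same unadjusted test: "a sample size of 2x 92 will achieve 80% power", "with estimated group standard deviations of 12.0 and 12.0", "with a significance level (alpha) of 0.05 using a two-sided two-sample t-test".

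In section 9, under Patient demographics and other baseline characteristics, baseline differences will not be tested. If they are considered clinically relevant, however, "the statistical methods may be modified to adjust for this difference". The same paragraph notes that such differences arise by chance.

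Under Randomisation, blinding and treatment allocation: "Randomization is performed using a table of random figures delivered by a independent party (clinical pharmacist), using envelopes with the treatment allocation". That section and Study procedures both have the envelope opened only after TSBL has been measured. BMI is an eligibility criterion, and sex is tabulated at baseline.

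**The concern.** Two things are at stake.

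- **Precision.** Baseline BMI, sex and TSBL are collected anyway and are known before the allocation is revealed. The trial's rationale is that variation in TSBL could matter for weight loss, and the protocol itself lists gender and baseline BMI as potentially relevant factors. A primary estimate that ignores them gives up whatever variance they explain.
- **An open primary model.** The clause on baseline differences does not say which variables count, how large a difference must be, which model would then be used, who decides, or when. Comparative analyses with deblinding by an independent person are planned at 1, 2, 3 and 4 years, all before the 5-year primary result. Nothing says the model is fixed before those looks.

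This is not simply a detail left to an analysis plan. The protocol states the primary test and, separately, permits an undefined departure from it.

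**Working it through.** **Inputs from the Sample size calculation.** Difference d = 5 points (40 against 35), SD 12 in each arm, two-sided alpha 0.05, 92 per arm; alternative SD of 9 in the active arm.

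**Step 1: reproduce the plan.** The noncentrality is d / (SD × √(2/n)) = 5 / (12 × √(2/92)) = 2.826. With 182 degrees of freedom the noncentral t gives 80.3% power (79.8% at 91 per arm), so 92 is right. With SDs of 12 and 9 the result is 88.9%, against 88.8% stated. Both figures reproduce.

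**Step 2: add fixed covariates.** Let R² be the share of %TWL variance explained by the covariates. The documents give no value, so it is an assumption. The residual SD is 12 × √(1 − R²). Three covariates leave 184 − 5 = 179 degrees of freedom. The equivalent unadjusted sample size is 92 / (1 − R²).

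| R² (assumed) | Residual SD | Noncentrality | Power, 92 per arm | Equivalent n per arm |
|---|---|---|---|---|
| 0 | 12.00 | 2.826 | 80.3% | 92 |
| 0.05 | 11.70 | 2.899 | 82.2% | 97 |
| 0.10 | 11.38 | 2.979 | 84.2% | 102 |
| 0.20 | 10.73 | 3.160 | 88.2% | 115 |

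**Step 3: what adjustment can cost.** The three lost degrees of freedom cost about 0.01 point. Chance imbalance in the covariates also inflates the variance of the adjusted estimate, on average by (184 − 3)/(184 − 3 − 3) = 181/178 = 1.017 for normally distributed covariates. At R² = 0 the noncentrality becomes 2.826/√1.017 = 2.802 and power 79.6%, a loss of about 0.7 point. At R² of 0.05, 0.10 and 0.20 the same correction gives 81.6, 83.6 and 87.6%. The loss is negligible even if the covariates are useless.

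**Step 4: compare the possible rules by simulation.** There were 92 per arm and two equally prognostic covariates, with 8,000 trials per null setting and 4,000 per alternative. The imbalance rule adjusts only for a covariate whose arms differ by more than 0.2 SD (an assumed threshold, since the protocol has none).

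| Total R² | Power, unadjusted | Power, imbalance rule | Power, fixed model | Type I, imbalance rule | Type I, fixed model | Type I, better of the two results |
|---|---|---|---|---|---|---|
| 0.05 | 80.9% | 80.9% | 81.9% | 4.8% | 5.0% | 6.3% |
| 0.10 | 80.8% | 81.8% | 84.3% | 4.5% | 5.1% | 6.6% |
| 0.20 | 80.3% | 82.3% | 87.2% | 3.9% | 5.0% | 7.2% |
| 0.30 | 80.1% | 84.6% | 92.3% | 3.2% | 4.8% | 7.3% |

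Monte Carlo standard errors are about √(0.05 × 0.95/8000) = 0.24 point for type I error and √(0.8 × 0.2/4000) = 0.6 point for power. The last column is the case in which both the unadjusted and the adjusted p-value are seen and the smaller is reported.

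**The case against.** The strongest reply is that nothing here is invalid. A two-sample t-test in a randomised trial is sound, it matches the sample-size basis, and the stated figures reproduce. That stands: the case for adjustment is one of efficiency and of closing an open clause.

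Four stronger readings are tempting, and the documents do not support them.

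- **That TSBL is a known predictor being wasted.** The Introduction says the contribution of residual bowel length has not been studied in this operation, and the Summary says only that the variation could have consequences. %TWL is also already scaled to initial weight. The covariates are plausible, not established. Limb length follows TSBL in the adjusted arm, which could flatten any relation there. If TSBL explained 10% of variance in the control arm and none in the other (assumption), a common slope would remove about 2.6% of pooled variance, worth about one point of power.
- **That the method would be changed after unblinding.** The clause gives no timing, so this is inference.
- **That the clause inflates the false-positive rate.** Its trigger is baseline difference, not outcome, and the simulated imbalance rule stayed at or below 5%. Inflation needs a choice made after seeing both results.
- **That the randomisation should be stratified by TSBL.** Unstratified allocation is no error. With the quoted median of 690 cm and SD of 94, z = (500 − 690)/94 = −2.02, or about 2% below 500 cm: some 5 of 212 patients. The protocol also quotes 2 to 3% below 400 cm, so the true share may be somewhat higher, but a separate stratum would be thin.

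It is also fair that the protocol does use these variables elsewhere, in the TSBL subgroup objectives (15 and 16) and the effect-modification model. Neither alters the primary estimate.

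**Conclusion.** The concern holds as a matter of efficiency and prespecification, not validity. The primary test is acceptable, but it leaves out baseline variables already in hand, and the clause on baseline differences leaves the primary model undefined in the circumstances where it would be invoked.

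The size depends on an R² the documents do not give. Over an assumed 0 to 20%, power at 92 per arm runs from 80.3% to 88.2%, or from 79.6% to 87.6% after allowing for chance imbalance. The benefit may be nil and the possible loss is under one point. The imbalance rule recovers only part of the gain: 82.3% against 87.2% at R² = 0.20. The type I error risk of roughly 6 to 8% is conditional on choosing between results already seen. The text does not rule that out, but does not plan it.

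**What to change.** In Primary study parameter(s), name one primary analysis: a linear model for 5-year %TWL with arm plus baseline BMI, sex and TSBL (continuous) as fixed covariates.

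- Use heteroscedasticity-robust standard errors in place of the Satterthwaite provision, since the plan itself anticipates SDs of 12 and 9.
- Keep the unadjusted t-test and the Mann-Whitney test as sensitivity analyses, so that a normality check no longer selects the primary method.
- The planned limb difference between arms grows with TSBL (0, 30 or 60 cm). State that the model estimates the average effect, and keep arm-by-TSBL as a separate analysis alongside objective 15.
- Use only pre-allocation covariates. Compliance, listed among the effect-modification factors, is not one.

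Under Patient demographics and other baseline characteristics, limit any imbalance-driven adjustment to sensitivity analyses.

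Reconcile Study design, which places randomisation at the start of the operation, with the two sections that have the envelope opened after TSBL is measured. TSBL is a clean baseline covariate only if it is recorded before the allocation is known.

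The cost is protocol wording. No extra patients, visits, measurements or change to the randomisation are needed. The change should be made before any comparative results are seen.
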